### Research governance

The research will be sponsored by Bangor University. The sponsor will ensure that appropriate indemnities are in place. The research will be overseen by a Trial Steering Committee and a Data Monitoring and Ethics Committee. Safety data will be routinely reported to the trial Data Monitoring and Ethics Committee (DMEC), and any suspected unexplained adverse reactions (SUSARs) noted will be reported to both the DMEC and the trial sponsor within established timeframes. Given the nature of the intervention, no interim analyses are planned, but such analyses may be requested at any time by the DMEC.

The issue of potentially competing studies will be monitored carefully. At the time of developing the protocol, only one study that could be perceived as potentially competing had been identified by local networks; that study was recruiting people with lower MMSE scores, and recruitment was due to be completed by May 2013. GREAT is a pragmatic trial and therefore participation would not preclude involvement in other clinical trials *per se*, unless those trials involved cognition-focused intervention. However, participant burden and inclusion/exclusion criteria in other, fastidious trials may preclude such dual participation. Each local PI will review any situation where there may be a conflict of recruitment pathways between trials to ensure that all potential participants are offered the most suitable option based on closest fit to eligibility criteria and participant preference.

### Service user involvement

Service users have been involved in the feasibility and pilot stages of the research leading to the development of this trial. The pilot trial benefitted greatly from the involvement of Alzheimer’s Society Research Network Volunteers. During the development of the present study we again sought, and took into account, the views of Alzheimer’s Society Research Network Volunteers and of service users contributing to the Dementia and Neurodegenerative Diseases Research Network (DeNDRoN) Patient and Public Involvement (PPI) programme. PPI for the GREAT trial will be provided through a partnership with the Alzheimer’s Society; this will ensure that service users are fully involved with the design, delivery and dissemination of the research. Service users will be consulted at each stage of the trial to ensure optimal tailoring of study protocols and procedures. To ensure that PPI is integrated throughout the study, two service user representatives will sit on the Trial Steering Committee. The Alzheimer’s Society Research Network will also contribute to dissemination activities towards the end of the study, ensuring that outcomes are communicated to lay audiences and policy-makers.

### Implementation within routine health-care provision

This will be the first multi-centre trial of individualised, goal-oriented cognitive rehabilitation for people with early-stage dementia. The CR approach offers a practical means of engaging people with dementia and carers in an early intervention process that aims to reduce functional disability and maximise engagement and participation, contributing to the possibility of living well with dementia. This approach can readily be offered by memory clinics in the period following diagnosis. Several UK memory services have already expressed interest in implementing CR. CR is also becoming acknowledged internationally; for example, it has recently been authorised for insurance reimbursement in Belgium, and has been conducted with the aid of trained volunteers in Canada. People with dementia have themselves begun to advocate for a rehabilitation approach
[79]. The trial will provide the necessary evidence base to extend these developments, if the findings demonstrate that CR is indeed both clinically beneficial and cost-effective. Towards the end of the trial, we will build on the experience gained at each site to demonstrate how the CR approach can most effectively be integrated into routine health-care provision. Once recruitment for the trial comes to an end, we will develop materials and offer training for clinical teams and therapists, as well as preparing information for people with dementia, carers and the general public. Information about good practice in this area will be disseminated through a range of routes.

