**Discussion:**

If the study confirms the benefits and cost-effectiveness of cognitive rehabilitation, it will be important to examine how the goal-oriented cognitive rehabilitation approach can most effectively be integrated into routine health-care provision. Our aim is to provide training and develop materials to support the implementation of this approach following trial completion.

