## Methods/design

This is a multi-centre single-blind randomised controlled trial comparing cognitive rehabilitation (CR) to treatment as usual (TAU) for people with early-stage Alzheimer’s, vascular or mixed dementia, with outcomes assessed at 3 and 9 months post randomisation. Participants will be recruited from memory clinics, old age mental health services and general practitioner (GP) practices. CR will be delivered in participants’ homes, with a carer involved where possible. The study will be run from the co-ordinating centre at Bangor University with six recruiting centres around the UK: North-West England, South-West England, West Midlands, London, South Wales and North Wales. At each recruiting centre, a part-time therapist (with an appropriate professional background, e.g. occupational therapy or psychology) will conduct the interventions, and a research assistant, blind to group allocation, will carry out assessments at baseline and at 3 and 9 months post-randomisation. Participants will be recruited to the trial between 1 April 2013 and 30 September 2015. A CONSORT-style flow chart for the trial is shown in Figure 
2.

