4. Practice in strategies for maintaining or improving attention and concentration.

5. A review of compensatory strategy use (e.g. calendars, diaries, reminder systems) and development and implementation of plans for improving strategy use, which might include increasing the efficiency of existing strategies and introduction of new strategies.

6. A review of current use of restorative strategies for retaining new information or improving recall, and practice in key strategies (mnemonics, semantic association, spaced retrieval), enabling participants to identify a preferred strategy and apply this in everyday situations.

In addition, to ensure sensitivity to the wider context, where appropriate a discussion of carer well-being and strategies for managing stress will be initiated, and information will be provided about additional sources of support and help, with encouragement to access these. The four maintenance sessions will focus on supporting maintenance of gains and encouraging continued goal performance and strategy use. The therapist will re-rate the extent of goal attainment following the session in week 14.

The effects of the CR intervention will be compared to treatment as usual (TAU). In the pilot, CR was compared with TAU and with an attention placebo condition (relaxation therapy). There was no evidence of a difference between the two control groups, which suggests that TAU can serve as an appropriate comparator. For the CR group, the CR will be provided in addition to TAU, while the control group will receive only TAU and will have no contact with the research team between assessments. TAU will consist of acetylcholinesterase-inhibiting medication where prescribed, and any other services normally provided apart from specific programmes of cognitive rehabilitation or other cognition-focused intervention. TAU may include, for example, routine monitoring by the Memory Clinic, information provision, attendance at drop-in groups or support groups, or carer participation in support groups. Service receipt during the intervention period, including dementia-specific services, monitoring and interventions provided by Memory Clinics, will be documented for all participants. All participants will be free to access services such as those offered by the Alzheimer’s Society, and the extent of this will be recorded.

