## Trial status

The GREAT trial started on 1 October 2012 and will be recruiting participants from 1 April 2013 to 30 September 2015. The end date for the trial is 31 December 2016.

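### Training in cognitive rehabilitation may be offered to clinical teams once recruitment closes, before the last 9-month assessments, and nothing keeps it from the services that provide treatment as usual

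*Protocol article*

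**What the plan says.** The section *Implementation within routine health-care provision* sets the trigger: "Once recruitment for the trial comes to an end, we will develop materials and offer training for clinical teams and therapists". The same sentence speaks of preparing, not releasing, information for the public. The Abstract's *Discussion* paragraph puts it differently: "Our aim is to provide training and develop materials to support the implementation of this approach following trial completion".

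The dates are in *Trial status*: the trial "will be recruiting participants from 1 April 2013 to 30 September 2015", and "The end date for the trial is 31 December 2016". *Methods/design* describes a trial "with outcomes assessed at 3 and 9 months post randomisation". Participants come from GP practices, old-age mental health services and memory clinics.

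In *The cognitive rehabilitation intervention*, TAU covers medication where prescribed and the services normally provided, "apart from specific programmes of cognitive rehabilitation or other cognition-focused intervention". That section and *Service utilisation* say that services received will be recorded for all participants.

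**The concern.** The trigger is the end of recruitment, not the end of follow-up. From October 2015 to about June 2016 the trial team may offer CR training while late-recruited TAU participants are still being followed. The implementation section names memory clinics as a natural setting for CR and reports that several services are already interested. These are the same kinds of service that provide TAU. Nothing in the article holds training back from them during that period.

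Any CR reaching TAU participants this way would act in one direction. It would narrow the difference between arms at 9 months, and the incremental cost with it. The principal analysis is by allocation, so the dilution would carry straight into it. The compliance analysis counts sessions completed, and the article does not say that this includes CR delivered to controls by outside teams.

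**Working it through.** **Inputs from the protocol article**
- Recruitment: 1 April 2013 to 30 September 2015, which is 30 months or 913 days (*Trial status*).
- Outcomes at 3 and 9 months (*Methods/design*). The last 9-month visit falls at about 30 June 2016.
- 480 randomised 1:1; 175 completers per arm for an effect of 0.3, alpha 0.05 and 80% power; 27% attrition (*Sample size*, *Procedure*). A two-sided test is assumed.
- Ten weekly CR sessions over 3 months, then four maintenance sessions (*The cognitive rehabilitation intervention*).

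**Assumptions, not in the article**
- Uniform accrual, varied below.
- The date on which training takes effect.
- The fraction of exposed controls who receive CR.
- The effect of that CR on them.

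**1. The plan's own figures.** n per arm = 2 × (1.960 + 0.842)² / 0.3² = 174.4, so 175. Then 350 / (1 − 0.27) = 479.5, so 480. Both reproduce. Power = Φ(d × √(n/2) − 1.960). With d = 0.3 and n = 175 this is Φ(0.3 × 9.354 − 1.960) = Φ(0.846) = 0.80.

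**2. Share awaiting an outcome when recruitment closes.**
- 9-month outcome: 9/30 = 30% (by days, 273/913 = 29.9%). That is 144 of 480, about 72 of them TAU, and 72/480 = 15% of all randomised.
- 3-month outcome: 3/30 = 10%, or 48 participants, about 24 of them TAU.
- If training starts 3 or 6 months later, the 9-month share falls to 20% (48 TAU) or 10% (24 TAU). At 9 months it is zero.

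**3. Sensitivity to accrual.** With cumulative accrual proportional to t^k, the 9-month share is 1 − (21/30)^k. This gives 22% for k = 0.7, 41% for k = 1.5 and 51% for k = 2. So 30% is the uniform-accrual figure, not a strict upper bound.

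**4. Dilution, immediate training with full effect.** Diluted d = 0.3 × (1 − s × u), where s is the share of controls exposed and u the uptake among them. With s = 0.30:

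| Uptake | d | Power at 175 per arm |
|---|---|---|
| 0% | 0.300 | 0.80 |
| 10% | 0.291 | 0.78 |
| 25% | 0.278 | 0.74 |
| 50% | 0.255 | 0.66 |

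**5. Counting only controls who could finish the ten sessions.** These take 3 months, so with a lag of L months the share is (9 − 3 − L)/30.
- L = 0: 6/30 = 20% (48 TAU).
- L = 3: 3/30 = 10% (24 TAU). Uptake of 25% gives d = 0.3 × 0.975 = 0.293 and power 0.78. Uptake of 50% gives d = 0.3 × 0.95 = 0.285 and power 0.76.
- L = 6: none.

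**6. Primary outcome.** *Sample size* reports a pilot effect above 1. Even the 15% dilution from step 4 (0.30 × 0.50) turns 1.0 into 0.85, and Φ(0.85 × 9.354 − 1.960) = Φ(5.99), which is near 1.

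**The case against.** The strongest reply is that the article gives a trigger and no roll-out date. It names materials before training, and it places the work on integrating CR into routine care near the end of the trial. The Abstract's reference to trial completion may attach only to implementation, in which case training during 2016 for later use fits both statements. Both arguments stand. A reader might infer a flat contradiction between the two sections, but the wording does not establish one. It is ambiguous and should be aligned.

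A reader might also infer that 30% of the sample would be contaminated, or that public information would be released early. Neither is supported. Only the TAU half can be contaminated, the article speaks of preparing information, and it gives neither a start date nor an uptake.

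Full effect is a harsh assumption too. Many exposed controls could not finish ten sessions before their 9-month visit. Baseline goals are passed to the therapist only for CR participants, so CR from an outside team need not target the goals that the primary outcome scores. This stands, and it makes the power figures in step 4 of the working near worst case.

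Two replies carry less weight. Recording services received would reveal exposure but not prevent it. The full protocol may say which teams are trained, and silence on that in an article would be no fault; but the article does state a trigger, and that trigger precedes the last outcomes.

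**Conclusion.** The point holds in a limited form. As written, CR training may be offered to clinical teams up to about 9 months before the last outcome is collected, and no section excludes the services providing TAU. That permits contamination biased towards no difference; it does not demonstrate it.

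Under uniform accrual about 72 TAU participants would be awaiting their 9-month assessment when recruitment closes. At an effect of 0.3 the loss runs from nil with no uptake, through power of about 0.78 or 0.76 with a 3-month lag and 25% or 50% uptake, to about 0.66 if training takes effect at once, half of the exposed controls receive CR and it works fully. The outcomes at risk are the secondary ones, sized at 0.3 with no margin, and the 9-month cost comparison. A primary effect near the pilot's would survive. The change is worth making because the risk runs in one direction and is cheap to remove.

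**What to change.** In *Implementation within routine health-care provision*, replace the end-of-recruitment trigger with wording such as: *Training in CR will be offered to services that care for trial participants only after the last participant's 9-month assessment is complete. Materials and public information may be prepared earlier but will not be released to those services before then.* Give the Abstract's *Discussion* paragraph the same trigger, so that its reference to trial completion cannot be read as a different date.

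Under this rule the share of controls exposed through trial-led training falls from 30% to zero, and planned power stays at 0.80. The cost is a delay of about 9 months in roll-out to those services. The last assessment is due at about June 2016, which leaves about six months before the stated trial end of 31 December 2016. The change protects the comparison only: training could still begin before the results are analysed, and whether to wait for them is a separate decision.

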## Trial status

The GREAT trial started on 1 October 2012 and will be recruiting participants from 1 April 2013 to 30 September 2015. The end date for the trial is 31 December 2016.

## Abbreviations

GREAT: Goal-oriented cognitive rehabilitation in early-stage dementia: study protocol for a multi-centre single-blind randomised controlled trial; PwD: People with dementia; AD: Alzheimer’s disease; CEA: Cost-effectiveness analysis; COPM: The Canadian Occupational Performance Measure; NWORTH CTU: North Wales Organisation for Randomised Trials in Health, Clinical Trials Unit; SOPs: Standard Operating Procedures; NIHR: National Institute for Health Research; CLRN: Comprehensive Local Research Network; MHRN: Mental Health Research Network; NISCHR CRC: National Institute of Social Care and Health Research Clinical Research Collaboration; DeNDRoN: Dementia and Neurodegenerative Diseases Research Network; PPI: Patient and Public Involvement; DMEC: Data Monitoring and Ethics Committee; BGSI: Bangor Goal-Setting Interview; GSES: Generalized Self-Efficacy Scale; HADS: Hospital Anxiety and Depression Scale; RBMT: Rivermead Behavioural Memory Test; TEA: Test of Everyday Attention; D-KEFS: Delis-Kaplan Executive Function System; RSS: Relatives’ Stress Scale; EQ5D: EuroQOL; WHOQOL-BREF: WHO Quality Of Life - BREF; CSRI: Client Services Receipt Inventory.
